## Discussion

This is a multicenter study assessing the potential benefits or harm of school doctors’ routine health checks and the use of questionnaires to identify children who would be likely to benefit most from a school doctor’s health check. The study aims to evaluate whether school doctors should routinely check all children at ages of seven and eleven, as is currently mandated by the law, or only the ones that adults are concerned about. If the need for a doctor’s health check, as evaluated from the study questionnaires, predicts the researcher-evaluated benefit gained from the health check the questionnaires may be suitable for screening in the future. At one year after the health check, the implementation of the school doctors’ interventions and follow-up plans will be analyzed, which enables us to evaluate the effects of school doctors’ work.

The strengths of the study include the usability and generalizability of the results in several ways: 1) The study is conducted in a normal clinical setting of the children’s regular health checks; 2) The doctors performing the health checks are blinded to the answers of the study questionnaires; and 3) The study includes schools and professionals from different municipalities and socioeconomic areas. The multi-informant approach may be helpful in identifying the need for support for both children and their families. A limitation of the study is that the developed questionnaires have not been widely tested. It is possible that the questionnaires function best in the Finnish school healthcare system since the organizational models of school health service systems differ greatly even within Europe [2]. Additional limitations are that children studying mainly in special education groups and children whose parents need an interpreter were left out. According to clinical knowledge, the school doctor’s assessment is frequently beneficial if the child’s special education needs have not been assessed in a specialist setting or if the child has not undergone a medical examination related to a new immigrant status.

The current Finnish school healthcare system offers equal service for all children in certain grades. The obligation to double check the children by both a nurse and a doctor leads to a situation in which most of the school doctor resources are allocated to health checks of asymptomatic children whom no-one is concerned about. Children in other year levels than grades 1, 5 and 8 receive very limited school doctor services. Many children with special needs, often related to social inequities, mental health and lifestyle related problems, could benefit from the school doctor’s attention earlier and more often than is currently recognized and offered. School doctors have little time for multidisciplinary work in student welfare groups and for cooperation with family counseling, child welfare and secondary care. This can result in inefficient care and referrals of patients from one unit to another. A structured screening method that would be available at any time of the year would increase the timeliness of the school doctor’s health check. If the finding of this study is that recognizing children most likely to benefit from school doctors’ appointments is impossible using the developed screening method, we have provided scientific evidence to support the current practice of school doctors’ routine health checks in Finland. However, more school doctor resources should be provided to school health care to ensure timely access to school doctors’ evaluation in case of need regardless of school grade.

The study will increase our knowledge of the benefits or harm of school doctors’ routine health checks and assess the developed screening method. We hypothesize that targeting the doctors’ health checks to the children in greatest need would increase the quality of school health services.

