**Fig. 1 Fig1:**
[figure not shown]
Current extensive health check in primary school grades 1 and 5 in Finland

**Table 1 Tab1:** Division of labor in school health services in primary school grades 1–6 in Finland^a^

Tasks	School nurse	School doctor
Extensive health examinations in grades 1 and 5	x	x
Collection of background information for the extensive health examinations	x	
Well Child Clinic (pregnancy and birth, biopsychosocial development)		
THL^b^ questionnaire by parent (1st and 5th grade), child (5th grade) and teacher (some schools)		
Statements from the student welfare group		
Evaluation: growth, vision, hearing, blood pressure, posture	x	
Complementation of background information		x
Evaluation of growth, somatic, psychiatric and neurologic status		x
Diagnostics and differential diagnostics		x
Vaccinations	x	
Referrals to physiotherapist, speech therapist, nutritionist	x	x
Referrals to secondary care		x
Guidance to or contact of specialized workers/other units	x	x
Teacher/special education teacher/school psychologist/school social worker		
Health center		
Family guidance center/Social worker/Home service		
Child welfare		
Referrals to laboratory tests	x	x
Referrals to medical imaging		x
Annual health checks (the general wellbeing, growth, eating, exercise and sleeping habits, friendships and hobbies)	x	
Prescriptions		x
Health education and support	x	x
Evaluation of special needs in all grades	x	x
Control visits	x	x
Participation in student welfare groups^c^	x	x

^a^Local variations may exist

^b^*THL* The National Institute for Health and Welfare

^c^Evaluate and develop the well-being of school community and students (permanent members: school principal, special education teacher, school psychologist, school social worker, school nurse)

The primary aims of this study are 1) to evaluate the potential benefits or harm of school doctors’ routine health checks in primary school grades 1 and 5 (at ages 7 and 11 years, respectively and 2) to explore whether some of the school doctors’ routine health checks in those grades can be omitted using study questionnaires that assess the parents’, school nurses’, and teachers’ potential concerns regarding each child. The secondary aim is to evaluate the implementation of the school doctors’ interventions and follow-up plans at one year after the health check.

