### Statistical methods

Sample size was calculated to detect 20% difference (25% vs 45%) in the benefit between children who need and children who do not need a doctor’s health check. Based on the pilot study, 25% of children who did not have a need for a doctor’s health check could benefit from one. To account for the clustered nature of the data, an intra-cluster (intra-school) correlation coefficient (ICC) of 0.06 was assumed. From each school, 25 children will participate from grade 1 and 25 children from grade 5. The required sample size is 450 children from both grades. Allowing for about 15% of missing data regarding the need for a health check and/or PREMs, the number of recruited children will be altogether 1050 from 21 schools.

Frequencies, percentages, means (with standard deviations; or in case of skewed distribution, medians with interquartile ranges) will be used as descriptive statistics.

Intrarater and interrater reliability will be assessed. KN will evaluate the need for the doctor’s health check and the benefit or harm of the doctor’s health check of each child and 200 randomly selected cases for intrarater reliability. To assess interrater reliability, SK will evaluate the data of 200 randomly selected children. SK will repeat the evaluation of the same 200 children to assess her intrarater reliability. Any discrepancies will be resolved using a third researcher.

The need for a doctor’s appointment and the benefit gained from it from the different people’s point of view will be compared. Researchers are blinded to study questionnaire responses when analyzing the benefit of the doctor’s appointment.

Multilevel logistic regression analyses will be conducted to account for the effect of covariates (e.g. doctors’ work experience and differences between municipalities). Analyses will be done separately for children from grade 1 and grade 5.

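### The stated test of the questionnaires is whether need predicts benefit, which puts no limit on the benefit missed if checks are omitted

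*Protocol article*

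**What the plan says.** At the end of the Background, the second primary aim is "to explore whether some of the school doctors’ routine health checks in those grades can be omitted using study questionnaires". The Discussion presents the choice as one between checking every child, as the law now requires, and checking only those about whom an adult is concerned.

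The article states one criterion for that choice, also in the Discussion: if need as assessed from the questionnaires "predicts the researcher-evaluated benefit gained from the health check the questionnaires may be suitable for screening in the future". The opposite conclusion, support for current practice, is tied to the finding that children likely to benefit cannot be recognised with the questionnaires.

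Statistical methods follows the same logic: "Sample size was calculated to detect 20% difference (25% vs 45%) in the benefit" between need and no-need children. The lower figure comes from the pilot: "Based on the pilot study, 25% of children who did not have a need for a doctor’s health check could benefit from one". The same section plans to compare need with benefit and to run multilevel logistic regression with covariates, separately by grade. Under Primary outcomes, need has three categories, the third being that a consultation may be enough. Table 2 grades benefit on a scale and does not dichotomise it.

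**The concern.** Whether a check can be omitted depends on what happens to the children who would no longer be seen: how many of them would have benefited, and what share of all benefit falls on them. A difference in benefit between need and no-need children, or an odds ratio, does not fix either quantity. With equal groups, 5% vs 25%, 25% vs 45% and 40% vs 60% all show the same 20-point gap, yet the share of benefiting children in the no-need group is 5/30 = 17%, 25/70 = 36% and 40/100 = 40%.

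So a result can meet the stated criterion while the questionnaires would leave many benefiting children unseen. This matters because the result is meant to inform whether legally required child health checks should continue for all. The design could answer the question directly: every child is checked and the doctors do not know the questionnaire answers, so the benefit rate among no-need children can be estimated without verification bias. The stated criterion does not refer to it.

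**Working it through.** **Inputs from Statistical methods.** Benefit 25% (no-need) and 45% (need); "an intra-cluster (intra-school) correlation coefficient (ICC) of 0.06 was assumed"; 25 children per school and grade; required size 450, read as per grade; 1050 recruited from 21 schools, that is 525 per grade.

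**Inputs not stated, so assumed.** Two-sided 5%, 80% power, equal groups.

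**Step 1: reproduce the 450.**
- Per group without clustering: n = [1.96·√(2·0.35·0.65) + 0.842·√(0.25·0.75 + 0.45·0.55)]² / 0.20² = 88.1, rounded up to 89.
- Design effect: 1 + 24 × 0.06 = 2.44.
- Total: 2 × 89 × 2.44 = 434.3, which is 17.4 schools of 25. Rounded up to 18 schools this gives 450 per grade.

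The figure is reproduced, but only after rounding up to whole schools. With an effective size of 450/2.44 ≈ 184, the power for 25% vs 45% is about 82%.

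**Step 2: what that planned-for result means for omission.** The benefit rate among no-need children is 25%, so the negative predictive value is 75%. Neither figure depends on the split.

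The share of all benefiting children who are missed does depend on it. With f the share classed no-need:

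missed = 0.25f / [0.25f + 0.45(1 − f)], and sensitivity = 1 − missed.

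| No-need share f | Missed | Sensitivity | Power at 450 |
|---|---|---|---|
| 0.2 | 12% | 88% | 61% |
| 0.3 | 19% | 81% | 74% |
| 0.4 | 27% | 73% | 80% |
| 0.5 | 36% | 64% | 82% |
| 0.6 | 45% | 55% | 81% |
| 0.7 | 56% | 44% | 76% |
| 0.8 | 69% | 31% | 66% |

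At f = 0.5: missed = 0.125/0.350 = 35.7%, and specificity = 0.375/(0.375 + 0.275) = 57.7%.

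**Step 3: how small a gap would be significant.** Take 225 vs 225 and a mean rate of 35%.
- With the full design effect: 1.96·√(2·0.35·0.65·2.44/225) = 13.8 points.
- If need is balanced within every school, the factor falls to 1 − 0.06 = 0.94 and the gap to 8.5 points.

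The second is a favourable case. The first matches the plan's own sample size.

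**Step 4: precision for the no-need rate.** Take 225 no-need children per grade, a rate of 25% and an ICC of 0.06.
- Over 18 schools (12.5 each) the design effect is 1 + 11.5 × 0.06 = 1.69, and the half-width is 1.96·√(0.1875·1.69/225) = 7.4 points.
- Over 14 doctors (about 16.1 each) the design effect is about 1.90, and the half-width is 7.8 points. Applying the school ICC to doctors is an assumption.

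**The case against.** The strongest reply is that this is hedged prose and not a decision rule. The aim is to explore, the Discussion says only that the questionnaires may be suitable, it lists limited testing as a weakness, and the article notes that current law does not allow checks to be omitted. Predicting is never defined as a significance test. Predictive values could well be reported under the planned comparison or set out in a fuller plan that is not shown. All of this stands, so the point is not that accuracy measures are missing. It is that the one criterion the article does state, with a sample size built to match it, does not fit the omission question. The hedge adds no limit on missed benefit.

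A reader might infer that the plan's own values imply the loss of about a third of all benefit. They do not. That figure needs the no-need share, which is not given; equal groups are suggested only by the back-calculation of the 450.

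A reader might also infer that the missed share is benefit truly lost. That is not established either. The article does not say where the graded scale was cut for 25% and 45%. Table 2 includes a level of little benefit, for which a nurse could have replaced the doctor. Nurses see all children every year, and some children in the consultation category would still reach a doctor.

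Finally, a ceiling on the no-need benefit rate is one reasonable criterion among several. The Discussion also cares about doctor time freed for children in greater need, so what is acceptable is for the study group to decide.

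**Conclusion.** The point holds in limited form. The article's only suitability criterion is an association, while the aim is omission, and an association puts no bound on benefit missed among omitted children. At the planning values the criterion would be met, with about 82% power at an equal split, by questionnaires under which one no-need child in four would have benefited.

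The 25% needs no assumption about the split. The 36% missed and 64% sensitivity hold only if half the children are classed no-need; the range is about 12% to 69% missed. All of these figures treat need as two groups and assume that the planning rates apply at the benefit cut-off finally used. The documents do not support the stronger claim that the plan would formally declare the questionnaires suitable on a significant result.

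**What to change.** Reword the criterion so that suitability for omitting checks is judged, in each grade, on the proportion of no-need children with researcher-evaluated benefit. State the cut-off; at least *Quite a lot* is one option that fits Table 2, where the criterion that a nurse could not replace the doctor sits at that level. Give a cluster-adjusted 95% confidence interval and compare it with an acceptable limit that the study group sets before need and benefit data are compared.

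Report sensitivity, negative predictive value and the share of checks saved beside it. Count the consultation group once as omitted and once as seen. The need versus no-need contrast can stay as planned, but should not by itself be taken to support omission.

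The cost is wording, one agreed limit and a little more analysis, with no new children or data. The claim becomes harder to meet. With about 225 no-need children per grade, the half-width at a 25% rate is roughly 7 to 8 points under an ICC of 0.06 at school or doctor level.

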## Methods

### Study design

This is a prospective, observational, multicenter study which is conducted by comparing the need for a doctor’s appointment based on the study questionnaires to the benefit or harm gained from the doctor’s appointment as assessed by the doctor, parent, child and researchers (Fig. 2). Under the current legislation in Finland, omitting some of the school doctor’s obligatory health checks and comparing groups of children who undergo a health check to children who do not undergo one cannot be done. To circumvent this problem, the school doctor’s check is arranged to all children, as usual, without knowledge of the content of the previously filled study questionnaires. At one year after the health check, the implementation of the doctors’ interventions and follow-up plans will be analyzed.

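### Failure of the questionnaires to identify the children who benefit would not be evidence for routine checks, yet the Discussion says it would

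*Protocol article*

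**What the plan says.** The sentence is in the Discussion of the protocol article. Its condition is a finding that "recognizing children most likely to benefit from school doctors’ appointments is impossible using the developed screening method". Its consequence is that "we have provided scientific evidence to support the current practice of school doctors’ routine health checks in Finland". Nothing else is required: not that benefit be common, not that it outweigh harm, and not that children without any concern gain from the check.

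The Study design section gives the structure behind any such finding. Under Finnish law, "comparing groups of children who undergo a health check to children who do not undergo one cannot be done". Instead, "the school doctor’s check is arranged to all children, as usual, without knowledge of the content of the previously filled study questionnaires". The outcome is "benefit or harm gained from the doctor’s appointment as assessed by the doctor, parent, child and researchers", so it is a judgement made after a check that every child has had.

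Statistical methods fixes the contrast: "Sample size was calculated to detect 20% difference (25% vs 45%) in the benefit between children who need and children who do not need", where need refers to the check by the doctor. The lower rate comes from the pilot, where "25% of children who did not have a need for a doctor’s health check could benefit from one".

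The Discussion also states the policy question: "The study aims to evaluate whether school doctors should routinely check all children at ages of seven and eleven", or only those about whom adults have concerns. Its limitations mention limited testing of the questionnaires, doubtful transfer to other health systems, and the excluded groups. They do not mention the absence of unchecked children.

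**The concern.** The sentence turns a negative finding about a screening tool into a positive finding about the practice that the tool was meant to replace. These are separate questions. Whether the questionnaires discriminate depends on the difference in rated benefit between need and no-need children. Whether routine checks are worthwhile depends on the level of benefit and harm and, for a causal claim, on what would have happened without the check. The condition in the sentence concerns only the first.

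At stake is what the study may claim about a statutory service. The Background says that a systematic review found too little evidence on school entry examinations, routine or selective, and that the Finnish system has not been evaluated for efficiency. A reader could take the sentence as filling that gap. If few children in either group benefited, the questionnaires would also fail to separate them, and the sentence would count this as support for checking everyone.

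**Working it through.** **1. The plan's own figure.** The sample size can be reproduced, so the point rests on no arithmetic error. Inputs from Statistical methods: 25% vs 45%, ICC 0.06, 25 children per grade per school, required size 450 (read here as per grade, since the grades are analysed separately), 1050 recruited from 21 schools. My assumptions, because the article gives none of these: two-sided alpha 0.05, power 80%, equal need and no-need groups.

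- n per group = [1.96·√(2·0.35·0.65) + 0.8416·√(0.25·0.75 + 0.45·0.55)]² / 0.20² = (1.322 + 0.555)² / 0.04 ≈ 88.1, so 89, or 178 in total.
- Design effect = 1 + (25 − 1)·0.06 = 2.44, and 178 · 2.44 ≈ 434.
- 434 / 25 = 17.4, so 18 schools, and 18 · 25 = 450 per grade.
- 21 · 50 = 1050 recruited, which allows 1 − 900/1050 = 14.3% missing, in line with the stated allowance of about 15%.

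**2. What the contrast can show.** Let p1 be the proportion with rated benefit among checked children with a need, and p0 the proportion among checked children without one. Failed screening means that p1 − p0 is near zero.

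| p1 | p0 | p1 − p0 | Conclusion under the sentence |
|---|---|---|---|
| 5% | 5% | 0 | supports routine checks |
| 25% | 25% | 0 | supports routine checks |
| 60% | 60% | 0 | supports routine checks |

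The rows differ greatly in what they suggest about checking every child, but the sentence treats them alike. A larger sample narrows the interval around zero and still does not tell the rows apart.

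**3. Other routes to the same finding.** If the questionnaires measure need poorly, or raters grade benefit inconsistently, p1 and p0 are pulled together even when some children gain much more than others. The sentence does not separate these cases from a true absence of difference.

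**4. What could tell the rows apart.** The level of benefit could, and the plan already collects it. With 450 children per grade and design effect 2.44, the effective number is 450 / 2.44 = 184.4. The 95% half-width for the overall proportion is 1.96·√(p(1 − p)/184.4): 3.1 points at 5%, 6.3 at 25% and 7.1 at 60%. For children without concern, taken as half the sample (92.2), it is 8.8 points at 25%. The sentence does not use this information.

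**5. What no quantity in the plan gives.** Every child is checked, so neither the level nor the difference is a contrast with no check. Keeping doctors unaware of the questionnaires protects the need-benefit comparison but creates no unchecked group.

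**6. Precision, as a side point.** Under the same assumptions the half-width for p1 − p0 is 1.96·√(2·0.25·0.75/92.2) = 12.5 points when both rates are 25%. Power is about 82% for 25% vs 45% and about 32% for 25% vs 35%. If only 20–30% of children fall in the need group (assumed range), power for 25% vs 45% is about 66–76%. Applying the full design effect is probably cautious, since both groups come from the same schools. A failure to separate the groups could therefore also reflect limited precision.

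**The case against.** The strongest reply is that the sentence compares two policies: check everyone, or check those whom the questionnaires select. The Discussion frames the question that way. If selection fails, this is some reason to prefer universal checks to selection by this tool. That much stands. It does not reach the stated conclusion, because a failed alternative is not evidence that the existing practice does good.

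Second, benefit and harm are a primary aim and a primary outcome, evaluated separately; percentages are planned, and every report of harm is examined individually. Uniformly low benefit would therefore be visible. Table 2 also asks whether a nurse could have replaced the doctor, which bears on added value. All this is true and makes the fix easy. But the sentence does not make its conclusion depend on any of it, and a rating after the check remains a judgement.

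Third, the article says openly why an unchecked comparison is impossible. It does, in Study design; the limitations and the disputed sentence do not carry that through.

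Fourth, this is Discussion prose and not an analysis rule. That is correct: no outcome, model or sample size depends on it.

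A reader might infer two stronger things that the documents do not support. One is that any non-significant need-benefit association would trigger the conclusion. The stated condition is that recognition is impossible with this method, which is a stronger finding, and Statistical methods does not equate it with a null test. The other is that every possible result leads to a policy conclusion. The positive branch is hedged: the questionnaires are said only to be possibly suitable for screening later. Unreliable rating is also anticipated, through planned intrarater and interrater assessment and by keeping researchers unaware of the questionnaire answers when they rate benefit.

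**Conclusion.** The inference is invalid as written. If the screening method fails, the study will have shown that these questionnaires were not shown to sort checked children by rated benefit. It will not thereby have produced evidence for routine checks.

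The size of the problem is logical and not numerical: zero difference at 5% benefit and at 60% benefit would receive the same conclusion, and no sample size changes that. The finding rests only on the stated condition and conclusion, the need versus no-need contrast, and the absence of unchecked children. It does not depend on the assumed alpha, power or group split, which enter only the side calculations.

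It is a fault of interpretation. Data collection, the planned comparisons and the sample size are unaffected. It is still worth correcting, because the sentence says in advance how one possible main result will be read on a question of public policy.

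**What to change.** Replace the sentence in the Discussion with wording such as:

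*If the questionnaires cannot identify the children who benefit, the study will conclude only that this screening method was not shown to be usable for selecting checks. Statements about routine checks will rest on the estimated proportions with rated benefit and harm, overall and among children without concern, with confidence intervals. These describe perceived benefit, because there is no unchecked comparison group.*

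Add the missing unchecked group to the limitations in the Discussion, referring to the legal reason already given under Study design. If the article can no longer be changed, put the same wording in the analysis plan or the results paper.

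The cost is wording only: the benefit and harm outcome is already planned, and no data, comparison or sample size changes. The downside is a less far-reaching conclusion if the screening method fails.
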